## **Aim 1. Data Collection Procedures**

*Aim 1. Overview of visit schedule:* Participants may complete 1-5 study visits, including enrollment (Table 2). A subset will complete an in-depth interview (IDI) on the Lead Risk Survey and lead point of care (POC) test experience (e.g., 2 separate visits). In addition, for participants with high BLL, there will be a home visit, an IDI on the home visit, and a blood lead level re-check visit (e.g., 3 additional separate visits).

| Table 2. Overview of Aim 1 procedures and data collection. | | | | | |
| --- | --- | --- | --- | --- | --- |
| Visit | Enrollment (N=350) | Lead risk survey & POC test IDI (subset, N=20) | Home visit  (all with high BLL; N~20) | Home visit IDI (all with high BLL; N~20) | BLL Recheck (all with high BLL; N~20) |
| Procedures | All: Lead POC test  If high BLL: Venous blood draw | Interview | Home observation and messages  Collect environmental media, in situ XRF lead detection | Interview | Lead POC test  Venous blood draw |
| D*ata collection* | *All: Demo-graphics*  *Lead Risk Survey* | *Understandability, acceptability of the Lead Risk Survey and POC test* | *Lead Risk Survey* | *Understand-ability, acceptability of messages on lead exposure reduction* | *Knowledge, attitudes practices (e.g., Recall of messages, behavior change)* |
| In-depth interview, IDI; point of care, POC; blood lead level, BLL; X-ray fluorescence detector. | | | | | |

### *Aim 1 Enrollment Visit:*

1. Enrollment data collection. Following informed consent, parents will provide locator information and will be administered a questionnaire on demographics.
2. A child lead POC test will be performed. Two drops of blood (a fingerstick sample) will be needed for the test. If the BLL is high, a confirmatory test will be done, involving 2 additional drops of blood. The POC test will be done suing a LeadCare II device or similar.

Study staff will ensure careful washing of the child’s hand with soap and water and air drying, prior to cleaning with alcohol. Using sterile technique, a microlancet and capillary tube will be used to prick the child’s finger and draw approximately 50 uL of capillary blood. This will be loaded into the LeadCare device for a near-instant reading (3 min).

***Threshold for defining high blood lead level (BLL):*** We plan to use the WHO reference level of ≥ 5 ug/dL to define children with high BLL and eligible for follow up procedures unless stakeholders suggest an alternative lower reference level be used. For children with BLLs equal to or exceeding the reference level, **a repeat confirmatory fingerstick BLL** will be conducted. This is a practice used in the United States when timely confirmation using venous sample testing using sensitive laboratory techniques is not readily available. In these cases, two POC results ≥ the reference level are used to confirm the child’s BLL is high.

1. Venous blood draw for anemia and future lead testing using sensitive techniques. For any child who has a POC test confirmed high BLL, a venous blood sample will also be collected. This will be used to check for anemia, and archived for in-laboratory batch analysis using sensitive standardized laboratory techniques. Anemia testing is important because iron deficiency can increase absorption of lead, exacerbating toxicity. In-laboratory sensitive assays are important to allow measurement of the change in BLL from enrollment. The LeadCare II assay is not designed for precise quantitative analysis and does not allow quantitation of BLLs below 3.3 ug/dL. The venous sample will be collected using standardized sterile technique by a trained pediatric phlebotomist. To reduce discomfort, we will use a topical anesthetic for the venous blood sample collection. The sample collected will be approximately 0.5-3 mL (approximately one teaspoon) from each child.

1. Exit. Participants with **low BLL** will be thanked for their time and exited following after receiving their results and post-test messaging, unless they have been selected for a Lead Risk Survey and Lead POC Test In-depth Interview.

### *Aim 1 Follow-up Procedures:*

Follow-up procedures will only involve children with high BLL. Briefly, participating parents of these children will be offered a home visit that includes environmental sampling (described below).

1. Home visit. Home visits will be conducted within 2-4 weeks of the lead POC test, or according to the parent’s preference or the study team’s capacity. During the home visit, procedures will include:
2. The Lead Risk Survey will be re-administered and a Home Observational Checklist will be used to identify and discuss residential features and items in child’s home environment that may be influencing the high BLL.
3. Tailored messages on lead exposure risk reduction will be provided.

As possible, items and media that are suspected contributors (e.g., soil near the home where the child plays/spends time, house dust, cooking pots and utensils, cosmetics, spices, toys, painted walls and surfaces) will be tested for lead in situ using an XRF device and documented with photos. These devices can measure lead safely in a variety of household exposure media including dust and soil, painted walls, cookware, children’s toys and clothing, and cosmetics. GPS coordinates will be obtained.

d. Environmental media samples (e.g., soil, the child’s main water source) will be collected for analysis.

1. Home Visit In-depth Interview (IDI). Home visit participants will be asked to participate in IDIs on understandability and acceptability of risk reduction messages and participant anticipated facilitators and barriers to uptake of recommended exposure reduction measures. This will be conducted on the same day or an alternate time based on participant preference. Interviews will be conducted as described above under *“Lead Risk Survey IDI.”*
2. BLL re-check visits. Participants with high BLL will be offered a return to clinic for BLL re-checks at 6 months post lead POC test (a natural timepoint for ABC participants). The re-check will be administered using the POC testing protocol described above. A venous blood sample will be collected.
   1. Referrals as described above will be made for any child who is found to have a newly identified BLL > 25 ug/dL.
   2. Parents will respond to standardized questionnaires to assess their knowledge of exposure risk factors discussed at the time of BLL testing and the home visit and uptake of recommended reduction measures.
   3. Participants will be thanked for their time and exited following after receiving their results and post-test messaging, unless a referral for BLL >25 ug/dl is required.

Data collected as part of Aim 1 may inform Aim 2. Any meaningful changes to the protocols or data collection tools developed through Aim 1 will be provided to the UW HSD and the KNH – UoN ERC for review and approval as a modification, prior to beginning Aim 2 study procedures.

AIM 2

## **Aim 2. Overview**

Parent-child pairs will be offered child lead POC testing. Pairs with a child with a high BLL will be randomized to two groups. Both groups will receive an in-clinic lead exposure risk reduction messaging protocol. One group will also receive an at-home lead exposure risk reduction messaging protocol.

## **Aim 2. Study Area Description and Study Site**

Recruitment and enrollment will take place at the Dandora II Health Centre, and the Baba Dogo Health Centere. We may also conduct recruitment at other similar health centres in Nairobi, such as the Kariokor Health Centre, the Kariobangi Health Centre and the Eastlands Health Centre in Nairobi. These sites were selected to prioritize sites with a range of potential lead sources and/or where the study team has established study sites. Babo Ndogo Health Centre is located in the Industrial Area of Nairobi, serving clientele with diverse industrial occupational exposure. Our current ABC cohort study has a study office at Dandora II Health Centre.

## **Aim 2. Study Population**

Aim 2 will involve parent-child pairs coming for routine well-child-clinic services (such as growth monitoring, childhood vaccines) at the public health facilities described above.

### *Inclusion criteria*

- Child age is 12 to 72 months
- Parent or primary caregiver that is a biological relative is available to give informed consent for LEIP study
- Parent/caregiver is 18 years of age or older or is an emancipated minor
- Available for 9 months follow-up
- Willing to allow the collection of blood from the child for a lead POC test
- Willing to be randomized to one of two intervention groups

### *Exclusion criteria*

- Unwilling to be contacted for the purposes of tracing and follow-up

## **Aim 2 Sample Size and Power**

*Sample size:* 1,500 children will be enrolled and undergo POC BLL testing. We anticipate this sample size is required to achieve N = 100 with high BLL (e.g., ≥ 5 ug/dL), based on estimated of high BLL in ABC child participants at age 12 months (8.2%). Should we achieve our target of N = 100 randomized prior to enrolling 1,500 parent-child pairs, we will stop enrollment early.

Parents of these children with high BLL will be randomized to immediate messaging tailored per in-clinic survey alone vs the same protocol along with a home visit for home observational checklist + reinforced messaging per home findings (N = 50 in each arm). Follow up visits at 3 and 9 months will include surveys of message recall, behavior change to reduce exposure, and a BLL recheck.

*Power:* Primary outcomes will be recall of survey identified exposure risk factors and self-reported uptake of risk reduction behavior. Assuming 5% attrition and 10% attrition at the 3 and 9 month re-check visits, respectively, we anticipate n = 95 and n = 90 at re-check visits, respectively. Assuming n = 90, alpha = 0.05, a one-sided test, and an observed recall or uptake of ≥ 67% within an arm, we will have ≥ 80% power to exclude a recall or uptake of < 50%. For an observed recall or uptake of > 43% within an arm, we will have ≥ 80% power to exclude the possibility that recall / uptake is actually < 25%.

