**Secondarily,** we will estimate the proportion of mothers (self-report on in-clinic surveys) and assessed homes with identified actionable targets, e.g., suspect household products, including cosmetics, chipped paint, potential occupational exposure, or other lead containing items observed using direct read instrumentation). We will describe the number and types of actionable targets identified for each participant. These data will enhance our adapted survey and messaging protocols for Aim 2. We will summarize descriptive statistics for standardized questionnaires on recall of identified risk factors, behavior change (e.g., proportions with recall of all or some factors vs. proportions with recall of some or no factors) and Risk, Ability and Attitude (e.g,, proportions with strong agreement vs. weak or no agreement). We will select questions with higher variability, and we will refine our questionnaires as appropriate for use in Aim 2.

**Aim 2 primary outcomes will be recall of risk reduction messages, and self-report risk reduction behavior. Exploratory outcomes will be uptake of the BLL re-check and change in BLL.** Balance between arms. We will compare baseline characteristics between randomization arms to evaluate balance of demographic and risk survey characteristics. We will use chi-square tests for dichotomous variables and rank sum tests or t-tests, as appropriate, for continuous variables.

**Recall of risk reduction messages and change in risk reduction behavior.** We will describe the proportion of parents with recall of all or most of their exposure factors identified on their surveys, within each arm and by child BLL. Similarly, we will describe proportions of parents self-reporting uptake of at least one of their risk reduction recommendations within arms and by BLL. We hypothesize that recall and behavior change will be moderate (e.g., greater than 50% in both arms), and that recall and behavior change will be highest for parents in the high BLL strata. Secondarily, we will explore potential differences in outcomes between arms, acknowledging that we will have limited ability to exclude small differences. Finally, we will describe the types of messaging recommendations taken up and not taken up by participants.

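### The Aim 2 power statement labels a within-arm calculation with the two-arm total (n = 90); each arm has about 45, where power at 67% versus 50% is about 70–78%, not 80% or more

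*Protocol*

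**What the plan says.** Protocol, Aim 2 Sample Size and Power, randomises parents of children with high blood lead level to two groups, "N = 50 in each arm". It continues "Assuming 5% attrition and 10% attrition at the 3 and 9 month re-check visits" and concludes "we anticipate n = 95 and n = 90 at re-check visits, respectively". The power sentence follows: "Assuming n = 90, alpha = 0.05, a one-sided test, and an observed recall or uptake of ≥ 67% within an arm", with at least 80% power claimed to exclude a rate below 50%. A second sentence makes the same claim for a within-arm rate above 43% against 25%. The test is not named.

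The Analysis Plan for Aim 2 describes recall and uptake within each arm. It hypothesises that "recall and behavior change will be moderate (e.g., greater than 50% in both arms" and treats the comparison between arms as secondary.

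**The concern.** The sentence joins two things that cannot both be true. The sample size is a two-arm total, while the proportion being tested belongs to one arm. No arm can hold 90 parents when 50 are randomised to it.

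This is the only power statement for the randomised trial, and it covers both primary outcomes. A reader who takes n = 90 at face value credits each arm with twice its sample. A reader who corrects it to 45 finds that the power stated for 67% against 50% is no longer reached. Neither can reproduce 67% and 43% as 80%-power thresholds from the inputs as written.

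**Working it through.** **Inputs (Aim 2 Sample Size and Power).** 50 randomised per arm; 10% attrition at 9 months; one-sided alpha 0.05 (z = 1.645); first pair p1 = 0.67, p0 = 0.50; second pair p1 = 0.43, p0 = 0.25.

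**Step 1: the sample size.** 100 × 0.90 = 90 in total; 50 × 0.90 = 45 per arm, with attrition equal between arms.

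**Step 2: formulas.** With s0 = √(p0(1−p0)/n) and s1 = √(p1(1−p1)/n):
- Wald: power = Φ((p1 − p0)/s1 − 1.645)
- Score: power = Φ((p1 − p0 − 1.645·s0)/s1)
- Exact: take the smallest r with P(X ≥ r | n, p0) ≤ 0.05; power = P(X ≥ r | n, p1)

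**Step 3: reproduce the plan's figures.** The rate needed for 80% power is:

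| | n = 90 | n = 45, Wald | Stated |
|---|---|---|---|
| against 50% | about 63–64% | 67.4% | 67% |
| against 25% | about 37–38% | 43.4% | 43% |

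Both stated rates match the n = 45 Wald thresholds rounded down. Neither matches n = 90, where power at 67% against 50% would be 93–96% and at 43% against 25% would be 96–98% on these three methods.

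**Step 4: 67% against 50% at n = 45.** s0 = √(0.25/45) = 0.0745; s1 = √(0.67 × 0.33/45) = 0.0701.
- Wald: 0.17/0.0701 − 1.645 = 0.780, power 78.2%
- Score: (0.17 − 1.645 × 0.0745)/0.0701 = 0.676, power 75%
- Exact: reject at 29/45 or more (actual alpha 0.036), power 70.4%

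The true rate needed for 80% power is 67.4% (Wald), 68.2% (score) or 69.1% (exact).

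**Step 5: 43% against 25% at n = 45.** s0 = √(0.25 × 0.75/45) = 0.0645; s1 = √(0.43 × 0.57/45) = 0.0738.
- Score: (0.18 − 1.645 × 0.0645)/0.0738 = 1.000, power 84.1%
- Exact: reject at 17/45 or more (actual alpha 0.039), power 80.4%
- Wald: 0.18/0.0738 − 1.645 = 0.794, power 78.6%

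**Step 6: observed versus true.** An observed 30/45 (66.7%) already excludes 50%: exact one-sided p = 0.018. Once a rate has been observed there is no power left to state. The 80% can only refer to an assumed true rate.

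**The case against.** The strongest reply is that nothing was miscalculated. Two separate thresholds both fall on the n = 45 Wald values, so the arithmetic was done per arm, and 90 is the retained total carried over from the preceding sentence. On that formula the shortfall is under 2 points and comes only from rounding 67.4% down to 67%. This stands, and it fixes the diagnosis as a labelling error.

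It can also be said that 80% is attainable at n = 45. The Wald z-test rejects from 28/45 (z = 1.69), and the probability of 28 or more at a true 67% is 80.1%. That is correct, so it would be wrong to say that no method reaches the figure. But the rule's actual one-sided alpha is 0.068, above the stated 0.05. The next cut-off, 29/45, brings alpha to 0.036 and power to 70.4%.

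The test is unnamed and may be set out in an analysis plan not seen here, and exact power is saw-toothed (74% at n = 44, 70% at 45, 67% at 46). The 70% should therefore be read as one end of a range.

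A reader might go further and multiply the arms' powers to say that the hypothesis of more than 50% in both arms has only even odds. The protocol does not support this. It describes proportions within each arm, sets no joint success rule, and claims power only within an arm. Nor does it claim power between arms: that comparison is secondary and made while "acknowledging that we will have limited ability to exclude small differences".

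**Conclusion.** The point holds as a wording and labelling error with a modest numerical consequence. The written n is twice the size of the arm it describes. At the correct 45 per arm, the claim of at least 80% power at 67% against 50% is missed by about 2 points (Wald formula), 5 points (score) or 10 points (exact), and is not met by a test that keeps alpha at 0.05. The 43% against 25% claim holds by score and exact calculations.

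This assumes equal attrition in the arms, a one-sample one-sided test at 0.05, and a true rate of exactly 67%. With no attrition (n = 50), power at 67% would be 81.9% (Wald), 79.0% (score) or 73.0% (exact), so attrition alone does not explain the gap.

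A reader might infer that the trial was sized on the wrong number and needs more participants. The agreement of both thresholds with n = 45 argues against that. Design, enrolment target, endpoints and analysis are unaffected. It should be corrected, but it does not threaten the trial.

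**What to change.** In Aim 2 Sample Size and Power:
- Replace n = 90 with n = 45 per arm (90 in total).
- Replace observed with true (assumed) in both power sentences.
- Name the one-sample test on which the power rests.
- Restate the 50% claim in one of two ways: 80% power at a true rate of about 68% (score, 68.2%) or 69% (exact, 69.1%); or about 75% (score) or 70% (exact) power at a true rate of 67%. Quote the threshold to one decimal or round it up, so that the rounding shortfall does not recur.
- Keep the 43% against 25% claim if the named test is score or exact. Under Wald, raise the rate to 43.4%.

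The cost is protocol wording and a slightly less favourable stated figure. No extra enrolment and no change to the analysis is needed.

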**Exploratory outcomes will be uptake of BLL recheck and change in BLL at 3 and 9 months.**

Return for a re-check. Return for a re-check visit is an indicator of parent awareness of importance of reducing lead exposure. We will summarize the proportions of parents returning for each BLL re-check visit for each arm, and compare to our benchmark of 50%, as for primary outcomes. We hypothesize that re-check will be high for both groups, and that re-check will be higher in parents with higher child BLLs. We acknowledge this outcome may have less variability across arms and may be subject to bias, given that participants will be provided a small reimbursement at each clinic visit.

We consider BLL change to be a distal indicator of effectiveness. In Lumumba et al,*^41^* standard deviations (SDs) were 15.5 ug/dL for maternal and 1.9 ug/dL for cord BLL. We anticipate that the SDs for child BLL will be lower than for adult women but higher than for cord samples.

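### The Aim 2 power statement conditions power on an observed rate; read as assumed true rates, 67% against 50% falls short of 80% power at 45 per arm

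*Protocol*

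**What the plan says.** The Protocol, under Aim 2 Sample Size and Power, randomises 100 dyads ("N = 50 in each arm"). On attrition it writes "Assuming 5% attrition and 10% attrition at the 3 and 9 month re-check visits" and concludes that "we anticipate n = 95 and n = 90 at re-check visits, respectively".

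The power calculation opens with "Assuming n = 90, alpha = 0.05, a one-sided test". It then says that for an "observed recall or uptake of ≥ 67% within an arm, we will have ≥ 80% power to exclude a recall or uptake" below 50%. A second sentence has the same form: "For an observed recall or uptake of > 43% within an arm, we will have ≥ 80% power to exclude the possibility" that the real rate is below 25%.

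The Analysis Plan sets no 67% or 43% criterion for the primary outcomes. It describes proportions within each arm and by blood lead level, and hypothesises rates above 50% in both arms. For return for a re-check it says it will "compare to our benchmark of 50%, as for primary outcomes". The protocol does not name the test behind the power figures.

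**The concern.** Power is the probability, before the data, that the test excludes the benchmark when the true rate takes a given value. Conditioning it on the observed rate leaves nothing to be probable: with n fixed, an observed count either excludes 50% at the stated alpha or does not. For example, 30 of 45 (66.7%) gives an exact one-sided p of 0.018, so 50% is excluded outright, not with 80% probability. The word appears in both sentences, and the second sets it against what the rate really is, so it is more than a stray slip.

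Two things are at stake. A reader cannot tell from the text what 67% and 43% are. And once they are read in the only way that works, one of the two power claims is too high for 45 parents per arm, by an amount that depends on the unnamed test.

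**Working it through.** **Inputs (Protocol, Aim 2 Sample Size and Power).** One-sided alpha 0.05, so z = 1.645. Fifty per arm less 10% attrition gives 50 × 0.90 = 45 per arm, 90 in total. The pairs are p1 = 67% against p0 = 50%, and p1 = 43% against p0 = 25%. Power rises with the true rate, so a claim for rates of 67% and above (or above 43%) stands or falls at the boundary value.

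**Step 1: reproduce the plan's figure (Wald, variance at p1).** Power = Φ[(p1 − p0)/√(p1(1 − p1)/n) − z].

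- 67% against 50%: standard error √(0.67 × 0.33/45) = 0.0701; 0.17/0.0701 − 1.645 = 0.780; power 78.2%.
- 43% against 25%: standard error √(0.43 × 0.57/45) = 0.0738; 0.18/0.0738 − 1.645 = 0.794; power 78.6%.

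Solving for exactly 80% gives true rates of 67.4% and 43.4%, which round to the printed 67% and 43%. So the printed rates behave as assumed true rates at 45 per arm.

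**Step 2: score test (null variance in the rejection limit).** Power = Φ{[(p1 − p0) − z√(p0(1 − p0)/n)]/√(p1(1 − p1)/n)}.

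- 67% against 50%: (0.17 − 1.645 × 0.0745)/0.0701 = 0.676; power 75.1%.
- 43% against 25%: (0.18 − 1.645 × 0.0645)/0.0738 = 1.000; power 84.1%.

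**Step 3: exact binomial test.** Take the smallest count c with P(X ≥ c | p0) ≤ 0.05, then power = P(X ≥ c | p1).

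- Against 50%: P(X ≥ 28) = 0.068 and P(X ≥ 29) = 0.036, so c = 29 (64.4%). Power at a true 67% is 70.4%.
- Against 25%: P(X ≥ 16) = 0.075 and P(X ≥ 17) = 0.039, so c = 17 (37.8%). Power at a true 43% is 80.4%.

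**Summary at 45 per arm, one-sided 0.05**

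| Test | Power, 67% vs 50% | True rate for 80% (vs 50%) | Power, 43% vs 25% |
|---|---|---|---|
| Wald | 78.2% | 67.4% | 78.6% |
| Score | 75.1% | 68.1% | 84.1% |
| Exact | 70.4% | 69.1% | 80.4% |

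**Step 4: where the test's boundary lies.** In the exact test, 29 of 45 already excludes 50% (one-sided 95% lower bound 51.1%), and 17 of 45 already excludes 25% (lower bound 25.7%). The printed 67% and 43% are therefore not the observed rates at which this test begins to exclude the benchmarks.

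**The case against.** The strongest reply is that this is loose wording with an obvious intended meaning. The rates sit in a list of planning assumptions, they reproduce to within two percentage points by Wald, and a statistician would read them as true rates. That stands as far as intent goes, and it is why the wording can be corrected safely. It does not make the printed sentences valid. Nor does it rescue the first power figure, which is below 80% under all three tests at 45 per arm.

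A second reply is that the claim would hold if n = 90 were the size of an arm: exact power would then be about 93% (reject at 54 of 90) and 98% (reject at 30 of 90). But both sentences speak of rates within an arm, and each arm has 50 before attrition.

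A third is that the protocol names no test and an analysis plan may properly do so. That is fair. No particular test is required here, only that the stated power match whichever is named.

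A reader might also infer something stronger: that 67% is a pass mark, that such a rule has only about 46% power at a true 67% (31 of 45 needed; about 59% if 30 of 45 is rounded up to 67%), and that an arm with 29 or 30 of 45 would be reported as missing its benchmark. The documents do not support this. Nothing in the protocol makes 67% or 43% a success rule, the Analysis Plan's benchmark is 50%, and an observed 64% lies above it.

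**Conclusion.** The point holds as a misstatement in the power paragraph, not as a fault in the design or in a decision rule. Power is wrongly conditioned on an observed rate in both sentences.

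Read as assumed true rates, the claim of at least 80% for 67% against 50% is missed by about 2 points (Wald), 5 points (score) or 10 points (exact). For 43% against 25% the claim is met by the exact and score tests and missed by about 1 point by Wald. Changing only the one word would therefore leave an incorrect power figure in print.

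This rests on 45 evaluable parents per arm at 9 months, one-sided alpha 0.05, and a one-sample test of each arm against a fixed benchmark.

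**What to change.** In both power sentences of Aim 2 Sample Size and Power:

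- Replace observed with assumed true.
- State that the calculation uses 45 evaluable parents per arm, 90 in total.
- Name the test.
- Restate the power to match it. With the exact test: about 70% at a true 67% against 50%, or 80% at a true rate of about 69%; and about 80% at a true 43% against 25%. If Wald is kept, 80% against 50% needs a true 67.4%, and 80% against 25% needs 43.4%.

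If an observed rate is to be quoted at all, give the boundary of the named test instead. With the exact test at 45 per arm, at least 29 of 45 (64%) excludes 50% and at least 17 of 45 (38%) excludes 25%, to be re-derived for the number actually followed up.

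The cost is two sentences of protocol text and a slightly less favourable stated power. Enrolment and data collection do not change.
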